### Phase 2: Validation

This second phase (ie, validation phase) aims to define the construct intended to be measured, providing evidence of psychometrics validity for each translated version of SCSE-OAC. Two main substeps will be performed (1) content and face validity and (2) construct validity.

According to the COSMIN guideline, the content validity of the scale will be assessed based on the key criteria of relevance, comprehensiveness, and comprehensibility. In other words, each item will be analyzed by patients and health care professionals for content, meaning, wording, and format. As per the relevance criteria, we will ask to judge the items’ relevance for the construct of interest (ie, SCSE) on a 4-point Likert scale (1=not relevant, 2=somewhat relevant, 3=quite relevant, and 4=highly relevant), with the following question

Please evaluate the relevance of the following self-care behaviors in managing your oral anticoagulation medication. Which behaviors do you find relevant to your daily life with OAC treatment?

Content validity index (CVI) will be computed at the item and overall scale (ie, I-CVIs and S-CVI), considering a critical threshold value equal to 0.70 for I-CVIs and 0.80 for S-CVI. For each native-speaking country, a minimum of 15 patients will be enrolled to participate in the study.

The patients’ eligibility criteria will be adult outpatients (18 years of age or older) with ongoing treatment with OAC at the time of the investigation, with a primary clinical indication for long-term OAC for NVAF, treated for at least 3 months, and who are willing to participate in the study. Instead, patients with cognitive decline (ie, Six Item Screener Test with lower than 4 points) will be excluded. Likewise, a convenience sample of 10 voluntary professionals from all relevant disciplines (ie, physician, nurse, and pharmacist) with documented clinical experiences in OAC for at least 1 year will be involved. Sociodemographic and professional variables will be considered to provide a sample description. Finally, an open-ended question will be included to assess the comprehensive and comprehensibility criteria. More specifically, participants will be asked to evaluate whether the items together comprehensively cover the construct of interest and if the population of interest clearly understands the items and response options to evaluate the face validity. The responses will be systematically analyzed, coded, and compared through a qualitative content analysis approach. Data collection will be done through an e-survey.

Following the achievement of content and face validity, 3 forms of validity will be tested—structural, cross-cultural, and criterion validity. As per the structural validity, we will assess the dimensionality of the construct to be measured (ie, SCSE) by factor analysis. However, no clear hypotheses about the underlying dimensions of the construct in the OAC population are available. Therefore, a 2-fold cross-validation will be performed for each language group, using explorative factor analysis (EFA) to explore relationships between observed variables and underlying factors and identify the most plausible psychometric structure and confirmatory factor analysis (CFA) to confirm the most plausible structure derived from EFA. More specifically, the overall sample for each language group will be randomly resampled to generate a subsample A for performing EFA (roughly 50% of the original sample) and subsample B for performing a CFA using the most plausible psychometric structure derived from EFA (using the second 50% of the original sample).

### Sample Size for Phase 2

In the field of factor analysis, the sample size estimation for allowing researchers to perform factor analysis properly is based on a rule of thumb supported by the Monte Carlo simulation study of enrolling 10 patients per item and per language group [25]. As a result, the final required sample size will be based on the version of the SCSE-OAM derived from the content validity phase because it depends on the number of items encompassed in the scale. Considering previous similar research in patients with heart failure, 10 items were developed for measuring SCSE for adults with heart failure. We hypothesized a similar number of items. In this case, 100 patients per language group will be necessary for EFA and subsequently for CFA.

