### Self-Care Self-Efficacy Framework

A self-care self-efficacy (SCSE) framework emerges as a valuable theoretical model for developing a measure of OAC-specific SE by being rooted in the middle-range theory of self-care for chronic illness [11,12] and Bandura’s [13] social cognitive theory. In this framework, the SCSE is the patient’s confidence in self-care maintenance (actions to maintain physiological stability), monitoring (efforts to detect signs and symptoms), and management (actions to address functional health behaviors) [14].

The SCSE framework can help researchers and clinicians effectively address OAC-specific challenges related to self-care behaviors in patients undergoing OAC treatment. This approach facilitates the creation of a theory-grounded SE scale that can discern and evaluate complex situations in the context of OAC. These situations involve the behaviors patients need to adhere to maintain physical and mental stability over time (maintenance), monitor signs and symptoms, and implement appropriate actions for symptom management (management) [11,12]. Consequently, the SE within this framework will assess a patient’s confidence in performing these demanding self-care tasks associated with OAC, encompassing decision-making processes, cognitive functioning, and overall health literacy [11,12].

For example, some behaviors investigated within the 3 domains of self-care may reflect how well patients respond to tailored education and preparedness. Other behaviors might address shared challenges in maintaining a healthy status, monitoring changes in the body and mental well-being while on OAC treatment, and making informed decisions in response to unexpected changes. As the project expands, these behaviors could be further tested and integrated into OAC-specific self-care measures. Therefore, developing the Self-Care Self-Efficacy Index in Oral Anticoagulation Therapy Management (SCSE-OAC) aims to offer a comprehensive and nuanced understanding of patients’ SE in managing their OAC treatment effectively by using and incorporating the SCSE framework.

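### The printed content-validity question asks about relevance to the rater's own daily life, not to self-care self-efficacy, the construct the I-CVI and S-CVI are meant to support

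*Protocol article*

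**What the plan says.** All of this is in the protocol article.

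- **Construct.** The section Self-Care Self-Efficacy Framework defines SCSE as the patient's "confidence in self-care maintenance (actions to maintain physiological stability), monitoring (efforts to detect signs and symptoms), and management". The object is confidence, not the behaviour itself.
- **Target of the rating.** Phase 2: Validation says raters judge the items' "relevance for the construct of interest (ie, SCSE) on a 4-point Likert scale", anchored from not relevant to highly relevant.
- **Question printed for that purpose.** It has two sentences. The first is "Please evaluate the relevance of the following self-care behaviors in managing your oral anticoagulation medication". The second is "Which behaviors do you find relevant to your daily life with OAC treatment".
- **Raters.** The same section says "each item will be analyzed by patients and health care professionals for content, meaning, wording, and format". For patients: "For each native-speaking country, a minimum of 15 patients will be enrolled to participate in the study". For professionals: "a convenience sample of 10 voluntary professionals from all relevant disciplines", chosen for clinical experience with oral anticoagulation (OAC).
- **Use of the ratings.** They give an item-level index (I-CVI, critical threshold 0.70) and a scale-level index (S-CVI, 0.80). Sample Size for Phase 2 bases the final sample on the version of the scale that leaves this step, at 10 patients per item and language group.

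**The concern.** The stated target and the printed question differ within one section. The target is relevance to a person's confidence in self-care. The question asks whether a behaviour has a place in the rater's own treatment and daily life. A patient can sensibly answer no to the second while the item remains important to the first. A behaviour tied to one type of anticoagulant, or to an uncommon event, is the obvious case. Measurements for Phase 2 records both direct and indirect OAC users, so differences in applicability are to be expected.

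The wording also addresses someone who takes the medicine. Professionals share the rating task but are selected for clinical experience, not for taking OAC. If they receive this text unchanged, they must either reinterpret it or answer literally.

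A smaller point is that the second sentence asks for a selection of behaviours, while the response scale asks for a grade on each one.

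At stake is what the I-CVI and S-CVI can be taken to show. They are to be reported as relevance to SCSE but would be computed from answers to a different question. Because the item count, and through it the recruitment target, depends on this step, an error here carries forward. Under the 10-per-item rule, each item kept or lost moves the requirement by 10 patients per language group.

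**Working it through.** The plan states no figure to reproduce here. The main check is to set the texts side by side.

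| Element | Stated target | Printed question |
|---|---|---|
| What is judged | Relevance to SCSE | Relevance of behaviours |
| Reference point | Patients' confidence in self-care | The rater's own medication and daily life |
| Confidence or self-efficacy named | Yes, through the definition of SCSE | No |
| Response asked for | Grade from 1 to 4 | First sentence: an evaluation. Second sentence: a selection |
| Raters it fits | Patients and professionals | Patients |

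The mismatch lies in text that the article prints in full, so condensation does not explain it.

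**Do other steps repair it?** The Phase 1 expert panel also rates relevance, but it rates OAC challenges and does so earlier. The open-ended question in Phase 2 covers comprehensiveness and comprehensibility, not relevance. Neither supplies the missing judgement on the construct.

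**Illustration of the possible size.** Inputs from the article: 15 patients per country, threshold 0.70.

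1. Ratings of 3 or 4 needed: 0.70 × 15 = 10.5, so 11. Check: 11/15 = 0.733 passes and 10/15 = 0.667 fails.
2. Assumption, not in the article: each patient independently has probability *v* of finding the item applicable, and only those patients rate it 3 or 4.
3. Chance of reaching the threshold: P(X ≥ 11), with X binomial(15, *v*).
4. At *v* = 0.50: (1365 + 455 + 105 + 15 + 1)/2^15 = 1941/32768 = 0.059.

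| *v* | Chance of reaching 11/15 |
|---|---|
| 0.30 | 0.07% |
| 0.40 | 0.9% |
| 0.50 | 5.9% |
| 0.60 | 21.7% |
| 0.70 | 51.5% |
| 0.80 | 83.6% |
| 0.90 | 98.7% |

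For comparison, if a question about the construct drew a 3 or 4 from 85%, 90% or 95% of raters (also an assumption), the same item would reach 11/15 with probability 93.8%, 98.7% or 99.9%.

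**If 15 patients and 10 professionals were pooled.** The article does not say that they are. The item would then need 18 of 25, since 0.70 × 25 = 17.5.

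- If all 10 professionals rate it 3 or 4, the patients must supply 8 of 15. At *v* = 0.50 that happens 50% of the time.
- If the professionals answer the printed wording literally and rate it not relevant, an item endorsed by every patient reaches only 15/25 = 0.60 and misses the threshold.

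**The case against.** The best defence is that the printed question is plainly the patient version. It appears just before the patient sample is described, professionals are introduced afterwards, and a condensed article may omit their wording. This stands in part. A reader might infer that professionals will receive this exact text and cannot answer it, but the article does not say so. It shows one question for a task given to both groups, so the point about professionals is conditional.

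Second, the scale is built from a list of self-care behaviours, and SCSE is confidence in performing them. Asking patients whether those behaviours matter to them is a reasonable part of judging content. Low applicability is also useful information for a short common scale (about 10 items are expected) that will be factor analysed across users of any OAC. This stands too. It would be too strong to say that the indices carry no evidence of content validity. Applicability is nonetheless a different judgement from the one promised, and the two should not share one score.

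Third, a reader might infer that items below 0.70 are automatically deleted, and that the monitoring and management domains would lose most. The article gives a critical threshold but no deletion rule. Rewording or discussion remains possible, and no item list is shown from which to predict losses by domain. The question on comprehensiveness also gives some protection against gaps in coverage.

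Finally, all-or-nothing ratings are an extreme assumption. With graded or hypothetical answers the effect shrinks quickly, as the rows for *v* = 0.80 and 0.90 show.

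**Conclusion.** The point holds as an internal mismatch. The article promises a rating of relevance to SCSE and prints a question about the rater's own treatment and daily life, without mentioning confidence. This follows from the text alone and needs no assumption.

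The consequence is a risk, not a demonstrated loss. Items that apply to only some patients could score low on the I-CVI for reasons unrelated to the construct. At 50% applicability and all-or-nothing rating, such an item reaches 11 of 15 about 6% of the time; across the range shown the figure runs from under 0.1% to almost 99%. The article gives no applicability share, no split by OAC type, no statement on pooling patients with professionals and no rule for items below threshold, so no single figure should be read as an estimate. The misfit for professionals depends on the wording being used unchanged.

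The correction is worth making before data collection, because ratings of a different question cannot be converted afterwards. They would have to be collected again.

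**What to change.** Replace the printed question with two parallel wordings on the existing 4-point scale, each shown with the item as it will appear in the scale:

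- **Patients:** *How relevant is this item to how confident a person taking OAC feels about carrying out self-care for the treatment, whether or not you have needed to do this yourself?*
- **Professionals:** *How relevant is this item to how confident a patient with NVAF on OAC feels about carrying out self-care for the treatment, whether or not the patients you see have needed to do this?*

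Delete the second printed sentence, the one that asks raters which behaviours they find relevant. Compute I-CVI and S-CVI from the new ratings only. If personal applicability is of interest, ask it as a separate question and keep it out of both indices.

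The cost is one reworded survey question and a professional version of it before the e-survey opens, possibly with a minor ethics notification. No extra participants are needed.

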### Data Analysis

The relevant number of factors to be retained in EFA data analysis will be done on the parameters of scree-test, parallel analysis, and factor rotation. More specifically, in the parallel analysis, if the eigenvalue of the original data’s factor is greater than the average of the eigenvalues of the parallel factor, that factor is retained. Likewise, the item retention will be assessed using factor loadings evaluations, where items with loadings >.40 will be retained. The structural model derived from EFA has to be used for both language groups in the CFA data analysis. The goodness of each model fit will be assessed based on the indexes of root-mean-square error of approximation (RMSEA; <.01) “excellent fit;” (<.05) “good fit;” (<.08) “mediocre fit;” comparative fit index (CFI) and Tucker-Lewis Index (TLI; >.90) and (>.95) [17,18]; SRMR (<.08) [19]; and chi-square test [25]. Furthermore, the multivariate normality of each model will be checked with the Mardia test, supposing that the multivariate skewness and kurtosis are significant. In the case of normality violation, a robust maximum likelihood estimator will be used.

After estimating the baseline model of scale for each language group, we will perform the Multi-Group Confirmatory Factor Analysis (MGCFA) to assess the cross-cultural validity. In other words, we will assess if the configural, metric, and scalar structure of SCSE-OAM is equivalent across 2 different language groups (English vs the Italian language). Achieving multi-group equivalence is pivotal to generating meaningful cross-group comparisons. Testing the measurement invariance means following a series of iterative analytical steps that bring from the largest model (where each language group has its parameters) to the more restricted one (where all the parameters are equal across the language group). This process stops when the model comparison is significant (ie, the large model fits the data significantly better than the more restricted one). A chi-square difference test will be performed to compare each model with the previous one to check whether a stronger invariance assumption holds. Data analysis will be performed in MPlus (Muthén & Muthén; version 8.1).

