## Results

The forthcoming validation of the SCSE-OAC is poised to significantly advance our understanding of SE in managing OAC among patients with NVAF. Anticipated results are expected to affirm the scale’s robust validity features, including its construct, criterion, and content validity, affirming its reliability across diverse patient demographics. Through exploratory and confirmatory factor analyses, the SCSE-OAC is projected to exhibit a coherent factor structure that aligns with theoretical expectations, reinforcing its use as a psychometrically sound tool for assessing SCSE in OAC.

Subsequent analyses are anticipated to unveil significant correlations between SCSE scores derived from the SCSE-OAC and key clinical outcomes, such as medication adherence rates, incidence of bleeding or thromboembolic events, and overall patient quality of life. These findings will underscore the critical role of SE in the self-management of OAC, suggesting that higher SE levels are associated with improved health outcomes and adherence behaviors. Moreover, the study is expected to elucidate the relationship between SE scores and sociodemographic characteristics, including age, education, and health literacy, providing valuable insights into how these factors may influence patients’ confidence and capabilities in managing their treatment regimens.

The significance of this study extends beyond the validation of a novel measurement tool. It promises to contribute substantially to the field of patient-centered care in anticoagulation management by offering health care professionals a reliable means to assess and enhance SE among their patients [1]. The SCSE-OAC will enable targeted educational and supportive interventions designed to bolster self-management skills by identifying, for instance, patients at risk of poor adherence due to low SE; therefore, mitigating risks associated with suboptimal treatment adherence. Furthermore, the scale’s validation across different languages and cultural contexts is anticipated to facilitate its global applicability, paving the way for its adoption in varied clinical settings and among diverse patient populations.

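### The S-CVI and the coverage judgement are fixed before the EFA removes items by loading, and no later step checks that they still describe the final scale

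*Protocol article*

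**What the plan says.** The framework section defines the construct as "confidence in self-care maintenance (actions to maintain physiological stability), monitoring (efforts to detect signs and symptoms), and management", so three domains are in view from the start.

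The section Phase 2: Validation puts content and face validity first. Patients and professionals rate each item's relevance, and indices are computed per item and for the scale, "considering a critical threshold value equal to 0.70 for I-CVIs and 0.80 for S-CVI". Comprehensiveness is judged on the set as a whole: "participants will be asked to evaluate whether the items together comprehensively cover the construct of interest". Then comes structural validity: "Following the achievement of content and face validity, 3 forms of validity will be tested". According to Sample Size for Phase 2, "the final required sample size will be based on the version of the SCSE-OAM derived from the content validity phase", so the set that enters the EFA is the set that was rated.

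Under Data Analysis the EFA applies one criterion to items: "items with loadings >.40 will be retained". The CFA, the invariance tests, the ROC cutoff and, in Phase 3, alpha and test-retest reliability all follow. None of these sections mentions the S-CVI or coverage again. The Results section expects the scale's validity to be affirmed, "including its construct, criterion, and content validity".

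**The concern.** An item's own content validity index survives the deletion of other items. The S-CVI and a judgement of comprehensiveness do not, because both are properties of a set. A factor loading measures variance shared with the other items, not how much of the construct an item covers. Phase 2: Validation also says that no clear dimensional hypotheses exist, so nothing ties the EFA to the three domains.

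If items are deleted, the content evidence on file therefore describes the longer pool and not the final scale. With about ten items over three domains, a few deletions could leave one domain thin or empty. The scale could still be reported with an S-CVI and a coverage judgement earned by the longer set. Developing and validating this scale is the primary aim.

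**Working it through.** **Inputs from the protocol article.** I-CVI threshold 0.70 and S-CVI threshold 0.80 (Phase 2: Validation); retention at loadings above .40 (Data Analysis); 10 patients per item and about 10 items (Sample Size for Phase 2); an EFA half of roughly 50% (Phase 2: Validation).

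**The plan's own figure.** 10 patients × 10 items = 100 per language group, which reproduces. The EFA has 50 patients if 100 is the whole language-group sample and 100 if it is per analysis. Both are used below.

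**Assumptions, not in the article.** Items split 4/3/3 over the domains; S-CVI as the average of the I-CVIs; the true loadings.

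**Step 1: can the S-CVI threshold be breached unseen?** S-CVI = (sum of I-CVIs) / k. With k = 10 and S-CVI = 0.80, the sum is 8.0. Deleting items whose I-CVI is 1.00 gives:

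| Deleted | S-CVI of retained items |
|---|---|
| 1 | (8.0 − 1)/9 = 0.778 |
| 2 | (8.0 − 2)/8 = 0.750 |
| 3 | (8.0 − 3)/7 = 0.714 |

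All are below 0.80, and every retained item can still be at or above 0.70. This is a worst case. Deleting an item at 0.70 would raise the index to (8.0 − 0.7)/9 = 0.811.

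**Step 2: random deletions.** The chance that at least one domain is emptied when items are deleted at random from 4/3/3:

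- 3 deleted: 2/C(10,3) = 2/120 = 1.7%
- 4 deleted: (1 + 2×7)/210 = 7.1%
- 5 deleted: (6 + 2×21)/252 = 19%
- 6 deleted: (15 + 2×35 − 1)/210 = 40%

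Fewer than three deletions cannot empty a domain.

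**Step 3: one weak domain.** One-factor principal-axis EFA, 2000 replicates, seven items with true loading .65. The share of EFAs in which the .40 rule empties the remaining three-item domain:

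| True loading in that domain | n = 50 | n = 100 |
|---|---|---|
| .50 | 1.4% | 0.3% |
| .45 | 4.6% | 2.5% |
| .40 | 12.6% | 12.3% |
| .35 | 22.7% | 35.3% |
| .30 | 41.4% | 58.5% |

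**Step 4: all items load equally.** Three correlated factors (0.3 or 0.6), normal data, parallel analysis against mean eigenvalues, principal-axis EFA with oblimin, items kept if any loading exceeds .40, n = 50 and 100, 400 replicates per cell. Ranges run over these settings.

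| True loading | At least one item deleted | A domain emptied |
|---|---|---|
| 0.7 | 4-35% | 0-2% |
| 0.6 | 58-82% | 2-8% |
| 0.5 | not tabulated | 17-20% |

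With 400 replicates, a rate of 5% has a standard error of √(0.05 × 0.95/400) = 1.1 percentage points.

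So a mismatch between the rated set and the final set is likely at moderate loadings, while outright loss of a domain is uncommon unless loadings are weak.

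**The case against.** - **This is a usual order, and an article may leave a re-check to the full protocol.** The order is indeed usual and is not faulted here. But the sequence and the retention rule are both stated, and the rule as stated carries no content condition. That is more than missing detail.
- **Deletion purely on loading is an inference.** The text states what is retained. It does not say that deletion is automatic or that judgement is excluded. This stands, and it is a reason to write the content review in.
- **The final scale is not claimed to be content-valid.** A reader might infer that the authors will certify a scale with a missing domain. The Results section states an expectation about anticipated findings, so that reading is not supported.
- **Frequent deletion is not loss of a domain.** A reader might take the 58-82% deletion rate at loadings of 0.6 as the size of the harm. The rate for an emptied domain is 2-8%.
- **Much of the simulated loss is under-extraction.** With factor correlation 0.6, parallel analysis kept fewer than three factors in 92-96% of replicates. With correlation 0.3, a domain was emptied in 0-3% of the replicates that kept three or more. This stands as to cause, but a check after the EFA would catch the loss whatever caused it.
- **The S-CVI measures relevance, not comprehensiveness.** Correct. Recomputing it is not enough, so a domain map is needed as well.

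**Conclusion.** The point holds in a conditional form. If the EFA deletes any item, the S-CVI and the coverage judgement no longer describe the final scale, and the plan as stated would not detect an S-CVI below its own 0.80 or a domain left without items. If nothing is deleted, the issue does not arise.

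The risk of a fully emptied domain is small when items load well. It exceeds 10% only when one domain loads at about .40 or below, or when all items load at about 0.5. These rates rest on the assumed 4/3/3 split and loadings; the S-CVI arithmetic rests on the averaging form and a pool that only just passes. The documents support neither the view that content validity should have been placed after the EFA nor a forecast that a domain will probably be lost.

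**What to change.** In Data Analysis, add a step after the EFA and before the CFA:

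1. Recompute the S-CVI on the retained items from the ratings already collected, and compare it with 0.80.
2. Map the retained items to maintenance, monitoring and management, and review on content grounds any deletion that would leave a domain without items.
3. If a domain is still lost, or the S-CVI falls below 0.80, report this and limit the content-validity statement to what the final scale covers.

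Do not require weakly loading items to be carried into the CFA. That would trade model fit for coverage, which is a matter for the content review and not for a fixed rule.

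The cost is a few lines of protocol text and minor extra analysis, with no new patient data. The possible downside is a less favourable S-CVI or a narrower claim.
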